### Intervention Interview

The intervention visit is an in-person session that may last up to 90 minutes and provides detailed instructions on the WITHWomen Pathways app and its features using a study-provided tablet. During this visit, the research coordinator will inform the participant that it differs from previous visits and that an interview or survey will take place at the end of the session, featuring different questions from those asked previously. In a private, mutually agreed-upon, safe location, such as a conference room or unoccupied office either at St Michael’s hospital, at one of our partner agencies, or in the community (eg, private meeting room at a public library), the research coordinator will provide instructions on how to use the tablet and engage with the WITHWomen Pathways web app. The participant will then be allowed to explore the web app freely, with the coordinator stepping back to provide privacy. The participant will be encouraged to spend a significant amount of time (up to 30 min) exploring the web app. This includes working through all service prioritization activities and creating an individualized safety plan. The coordinator will check in periodically to answer questions. It will be explained to the participant that each time she uses the web app, it is considered a new session, and that for safety reasons, the web app does not store or restore data previously entered. After she has explored each section of the web app, the research coordinator will ensure that the participant is able to access the WITHWomen Pathways app on her own device and is comfortable using and exiting the web app from that device as well. Once the participant is comfortable and familiarized with the app, the session can be concluded. Then, the intervention visit survey will be administered using the interview guide and visual aid (available upon request). Finally, the interviewer will schedule the first remote follow-up interview and thank the participant for her time and input. Participants will be allowed and encouraged to use the web app as often as they like during and after the follow-up period.

### Postintervention Interviews

Following standard SCED protocols, the postintervention assessments use the same questionnaires and intervals as the preintervention assessments [28]. At the first postintervention assessment (scheduled during the intervention interview), the participants will complete the same outcome measures at the same intervals (every 3‐4 days) as in the preintervention assessments. Participants with children will also complete the perceived child well-being questionnaire at the final visit. All participants will complete the same number of postintervention assessments (n=8) over the course of 4 weeks after their intervention interview. Postintervention interviews can be conducted in person, via telephone, or using the online survey.

### Strategies to Prevent Attrition

Given the high participant burden of SCED and the potentially precarious position in which many women experiencing IPV find themselves, attrition from the study is likely. However, the research team has devised strategies to safely encourage participants to remain in the study. First, the study is designed to be as convenient for participants as possible, offering several modes of contact (in person, via telephone, and online), evening and weekend assessment options, and face-to-face interviews at partner organizations convenient to the participant. Compensation will also be given at the point of assessment, within a day following each check-in, and each assessment will be scheduled at the end of the preceding visit. For those who do not attend previously scheduled assessment visits, researchers will first reach out via the safe contact methods indicated by the participant at different times of the day. They will then search for updated information or attempt previously disconnected phone numbers before reaching out to the safe contacts listed by the participant. While resource limitations prevent us from overenrolling to guard against attrition, sample size is only one of several levers that SCED studies (as opposed to traditional evaluation designs) can use to improve statistical power. Should attrition become an issue, we will explore using additional baseline and follow-up measures in the remaining participants, simulating power using different effect size estimates, and assessing the number of outlier scores to understand its effect on generalizability [50].

### Managing Minor Emotional Distress

Given the topic of IPV, study population, and sensitivity of the assessment questions, researchers will undergo training on how to handle situations where participants experience emotional distress during interviews. Sufficient time will be allocated during the initial interview to address any questions or concerns, including the potential for anxiety. For telephone or in-person surveys, researchers will help participants devise a step-by-step strategy to manage various scenarios, such as how to respond if they start crying or feel uncomfortable answering a question. Participants will also discuss options for managing anxiety during the interview ahead of time, such as deep breathing or temporarily discontinuing the interview. For online links, participants will be asked to complete the survey only when they are alone, and all participants will be provided with links to mental health resources at the end of the survey. The research coordinator will be in regular contact with all participants. Researchers will also note the PHQ-4 scores of all participants and those with elevated depressive and anxiety symptoms, making sure to carefully monitor these participants specifically and provide contact information for community mental health resources. Any adverse events beyond minor emotional distress will be immediately reported to the Research Ethics Board and integrated into our assessment of the safety of using SCED for IPV interventions.

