**Figure 1. F1:**
[figure not shown]
Overview of a typical single-case experimental design study flow.

SCED has been used in medical, psychological, and behavioral research for decades to better understand the mechanisms of intervention effects. Recently, it has also been used to assess the effectiveness of technology-based interventions in other areas [32], for example, in vulnerable populations such as adolescents experiencing psychological distress [33], individuals with serious mental illness [34,35], adults with severe autism spectrum disorder [36], and young children [37]. The extant literature suggests that SCED is a viable alternative to RCTs, especially for sensitive outcomes, because it allows for closer observation of individuals [38]—something which is critical for ensuring the immediate safety of participants living with IPV [26,27]. However, to the best of our knowledge, this will be the first adaptation of the methodology to IPV studies [32].

To gauge whether SCED is a viable approach for evaluating a web-based safety planning tool for English-speaking women in the GTA, we have established the following study objectives:

To understand whether women who are living with or have recently experienced IPV can be safely engaged for intense follow-up for the purpose of evaluating a safety planning interventionWe hypothesize that our safety protocols and individualized approach will allow for safe participation in the study, as measured by a lack of reportable or adverse events.To examine the preliminary effectiveness of WITHWomen Pathways and our novel safety protocols on 3 primary and 2 secondary outcomes of interestWe hypothesize that within-person changes to decisional conflict and depressive symptoms will show a decrease, whereas empowerment to take safety actions will demonstrate an increase.

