### Preintervention Assessments

As previously discussed, SCED requires the establishment of stability in a given outcome measure prior to intervention delivery [40]. We plan to assess 3 primary outcome measures that align with those assessed by previous RCT safety planning evaluations and are the direct targets of the intervention’s activities: safety self-efficacy, decisional conflict, and confidence in planning (see Table 1). These speak to the goals of safety planning, which are to *prime* those who are currently experiencing IPV to take action to improve their safety, which reflects the often nonlinear paths and ambivalence women feel about extricating themselves from a violent relationship [41,42]. Additionally, we plan to measure 2 secondary outcomes: IPV recurrence and mental health. IPV itself is a secondary outcome because changes in IPV exposure are not necessarily expected, for the reasons mentioned above. While mental health is not directly targeted by intervention activities in WITHWomen Pathways*,* participation in the intervention may secondarily lead to improvements in mental health through help-seeking actions.

**Table 1. T1:** Outcome variables for evaluation of *WITHWomen Pathways*.

Outcome measured	Primary/secondary	Instrument	Reference
Use and perceived helpfulness of safety strategies, service use	Primary	Intimate Partner Violence Strategies Index (adapted)	Goodman et al (2003) [43]
Empowerment related to safety	Primary	MOVERS^a^	Goodman et al (2014) [13]
Decisional conflict	Primary	Decisional Conflict Scale	O’Connor (1995) [12]
Anxiety and depression symptoms	Secondary	PHQ-4^b^	Kroenke et al (2009) [44]
Intimate partner violence	Secondary	Composite Abuse Scale-Short Form	Ford-Gilboe et al (2016) [45]

a MOVERS: Measure of Victim Empowerment Related to Safety.

b PHQ-4: Patient Health Questionnaire-4.

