### Data Analysis Plan

Following the SCED technical guidance published by the What Works Clearinghouse (WWC) of the US Department of Education’s Institute for Education Sciences [49], we will begin by computing descriptive statistics for each outcome measure, stratified by participant and intervention phase. For each scale, we will calculate the number of observations, mean, SD, SEM, minimum, and maximum, separately for the preintervention and postintervention periods. This will allow us to summarize overall patterns and assess changes in central tendency and variability over time.

The WWC also recommends visual inspection of data points and trend lines to gauge preintervention and postintervention effects [52]. To visualize the within-person patterns over time, we will create scatterplots for each participant and outcome measure, overlaying fitted linear trend lines for both the preintervention and postintervention phases. This will allow for visual inspection of potential shifts in level and trend following the intervention. A vertical reference line will denote the point of intervention onset.

Internal consistency will be assessed using Cronbach α, calculated on the basis of the preintervention responses for each scale described previously. These estimates will provide an indication of scale reliability prior to any intervention effects.

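### Elevated PHQ-4 scores prompt a staff response while PHQ-4 is also an outcome, and the planned analysis cannot separate that response from an app effect on PHQ-4

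*Protocol article*

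**What the plan says.** All references are to the Protocol article.

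- **The trigger.** Managing Minor Emotional Distress: "Researchers will also note the PHQ-4 scores of all participants and those with elevated depressive and anxiety symptoms". The article states no cutoff and does not restrict this to one phase.
- **The response.** The same sentence continues: "making sure to carefully monitor these participants specifically and provide contact information for community mental health resources".
- **What every woman gets.** The same section: "all participants will be provided with links to mental health resources at the end of the survey". The coordinator also stays in regular touch with everyone.
- **PHQ-4 as outcome.** Table 1 lists "Anxiety and depression symptoms", measured by PHQ-4, as secondary. The objectives at the end of the Introduction expect that "within-person changes to decisional conflict and depressive symptoms will show a decrease". Preintervention Assessments gives the route: "participation in the intervention may secondarily lead to improvements in mental health through help-seeking actions".
- **Service use as outcome.** One primary outcome in Table 1 is "Use and perceived helpfulness of safety strategies, service use", from an adapted index.
- **The analysis.** The Introduction makes each participant's baseline her control. On the plots, "A vertical reference line will denote the point of intervention onset"; no other event is described. The Data Analysis Plan compares the phases by Tau-U, unadjusted and adjusted for baseline trend.

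**The concern.** In a within-person before-after design, anything else that changes near the start of the app competes with the app as an explanation. Here one such event is part of the study's own conduct, and the outcome itself sets it off. A woman whose PHQ-4 is elevated is watched more closely and given mental health contacts. If that helps her, her PHQ-4 falls, which is the direction expected of the app. The route is similar too: the article explains a mental health gain by help-seeking, and handing over contact details also prompts help-seeking, but from staff.

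At stake is what a fall in PHQ-4 may be taken to show. A response late in baseline or during follow-up puts its effect into the postintervention phase. A response early in baseline that acts fast puts its effect into the control phase, where it could take up improvement that the app would otherwise have brought. Without dates, a reader cannot tell which case applies to which woman.

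**Working it through.** The plan has no figure of its own to reproduce on this point. The check is structural, followed by an illustration of possible size.

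**Step 1: when can the response occur?** There are 5 to 8 baseline and 8 postintervention assessments (Preintervention Assessments; Postintervention Interviews), so 5 + 8 = 13 to 8 + 8 = 16 occasions. Five baselines at 3- to 4-day intervals span 4 × 3 = 12 to 4 × 4 = 16 days. A response prompted in baseline can therefore take effect after the app has started. The stability rule needs only one measure to be stable, so PHQ-4 may still be moving at that point.

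**Step 2: can Tau-U tell the two apart?** With a fall in PHQ-4 counted as positive:

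- Unadjusted Tau-U = S_AB / (n_A × n_B)
- Adjusted Tau-U = (S_AB − S_A) / (n_A × n_B)

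S_AB is improving minus worsening pairs between phases, and S_A is the same count within baseline. The adjustment removes only what already shows as trend within baseline. A response at the last baseline or later leaves no mark on S_A, so nothing is removed.

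**Step 3: possible size.** Simulation with n_A = 5, n_B = 8 (40 pairs), 3000 series per scenario and **no app effect**. Assumptions that are not in the documents: score range 0 to 12, true level 8, within-person SD 1, and a response that lowers PHQ-4 by 1 or 2 points, either in full from the next assessment or evenly over the next four. The response is placed at a fixed assessment, not triggered by the simulated score. Mean adjusted Tau-U:

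| Response at | 1 point, at once | 1 point, over four | 2 points, at once | 2 points, over four |
|---|---|---|---|---|
| Baseline 1 | 0.05 | 0.20 | 0.07 | 0.33 |
| Baseline 3 | 0.22 | 0.37 | 0.35 | 0.63 |
| Baseline 5 | 0.50 | 0.41 | 0.81 | 0.69 |
| Postintervention 1 | 0.42 | 0.33 | 0.71 | 0.57 |
| Postintervention 3 | 0.30 | 0.22 | 0.51 | 0.38 |

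Without any response the mean is 0.01. Single series then reach 0.20 by chance in about 30% of cases and 0.60 in 3 to 4%.

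The article's benchmarks are small 0.20–0.59, moderate 0.60–0.79 and large ≥0.80. A response at the fifth baseline thus averages small (1 point) to moderate or large (2 points) with an app that does nothing. At the first postintervention assessment it averages small to moderate. At the first baseline with immediate action, almost nothing is left.

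The simulation contains no app effect, so it does not measure masking. That part rests on reasoning: masking arises if the early response takes up improvement that the app would otherwise have produced.

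**Step 4: weight of one woman.** 1/6 = 17% of the planned cases; 1/4 = 25% of those analysed so far.

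**The case against.** **The score-triggered increment is modest.** All women get resource links and regular contact, and they are recruited through service organizations. What elevated scores add is closer watching and contact details. A reader might call this a referral to treatment, but the text does not say that. This limits the likely size. It does not remove the problem, because the extra step is tied to the outcome and can begin at any assessment.

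**Records may exist elsewhere.** The article mentions a separate safety protocol, available on request, which may well require dated notes. That stands, and missing records are not alleged. The point concerns the analysis that is described, where nothing uses such dates.

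**Attribution is already hedged.** Mental health is described as not directly targeted, significance testing is disclaimed, the trial is called preliminary, and Study Limitations lists confounding from the absence of randomization. All true. But that caveat is general, its remedy is deferred to later studies, and it does not name this mechanism. The plan also treats even small effects as potentially meaningful when the visual pattern agrees.

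**Stronger readings that the documents do not support:**

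- *Regression to the mean.* One might infer that selecting high scores builds in a fall. The trigger decides neither who is analysed nor when the app starts; that follows the stability rule or the cap of 8 baselines.
- *Inflation only.* The bias can run either way, depending on timing.
- *A perfect spurious effect.* If all 40 pairs improved, Tau would be 40/40 = 1.0, but nothing shown suggests that contact details would do this.
- *A compromised primary outcome.* Service use is named in Table 1, but the adapted items are not shown and no direction is hypothesized for it. An influence is possible but less certain. Nothing here implicates decisional conflict or empowerment.

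**Conclusion.** The point holds for PHQ-4. It is both a secondary outcome with an expected fall and the trigger for an added staff response, and neither the plots nor Tau-U as described can separate that response from the app when it starts late in baseline or during follow-up. A fast-acting response early in baseline could instead mask an app effect. For service use, an influence is possible but not established.

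The documents do not fix the size. The simulated averages of 0.33 to 0.81 for a response at the fifth baseline or first postintervention assessment depend on the assumed 1- to 2-point fall, level and SD, and show only what could happen. How many women had elevated scores is not stated.

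This is a cheap improvement to what can be concluded about PHQ-4. It is not a fault in the safety procedure and not a reason to doubt the study as a whole.

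**What to change.** Leave the safety response unchanged and add the following:

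1. Record the date and type of each score-triggered contact. For the 4 women who have completed the study, reconstruct this from study records where possible.
2. Mark each such contact on that woman's PHQ-4 plot, beside the line for the start of the app.
3. In the Data Analysis Plan, add a sensitivity report of PHQ-4 Tau-U with and without affected women, keeping all women in the main analysis. Setting affected women aside in the main analysis would select on the outcome and favour those with least room to fall.
4. In Study Limitations, name this co-intervention as a limit on attributing PHQ-4 change to the app.

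The cost is slight extra record-keeping, one more mark on some plots and a more cautious PHQ-4 conclusion. Records for the completed women may be incomplete; if so, say so.

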### IPV Reporting Requirements

Health care professionals and staff affiliated with St Michael’s Hospital or the University of Toronto are not legally or professionally obligated to report suspected or verified partner violence. However, reporting child abuse is mandatory under Ontario’s Child and Family Services Act, Section 125 [51]. Participants will be informed during the interview’s informed consent instructions that the interviewer is obligated to report child abuse, allowing them to control the disclosure of any such incidents.

### Data Analysis Plan

Following the SCED technical guidance published by the What Works Clearinghouse (WWC) of the US Department of Education’s Institute for Education Sciences [49], we will begin by computing descriptive statistics for each outcome measure, stratified by participant and intervention phase. For each scale, we will calculate the number of observations, mean, SD, SEM, minimum, and maximum, separately for the preintervention and postintervention periods. This will allow us to summarize overall patterns and assess changes in central tendency and variability over time.

The WWC also recommends visual inspection of data points and trend lines to gauge preintervention and postintervention effects [52]. To visualize the within-person patterns over time, we will create scatterplots for each participant and outcome measure, overlaying fitted linear trend lines for both the preintervention and postintervention phases. This will allow for visual inspection of potential shifts in level and trend following the intervention. A vertical reference line will denote the point of intervention onset.

Internal consistency will be assessed using Cronbach α, calculated on the basis of the preintervention responses for each scale described previously. These estimates will provide an indication of scale reliability prior to any intervention effects.

To quantify the pre-post changes in outcomes for each participant, we will follow the WWC guidance by calculating Tau-U, a nonparametric effect size metric. Tau-U allows for the estimation of intervention effects while accounting for trends that may be present during the baseline (preintervention) phase [53,54]. For each outcome and participant, we will compute (1) Tau (preintervention, A), to evaluate baseline trend; (2) unadjusted Tau-U (A vs postintervention, B), which compares data points between the baseline and postintervention phases without adjusting for baseline trend; and (3) adjusted Tau-U (A vs B), which corrects for any nonrandom trends in the baseline phase. Consistent with Fingerhut et al [54], our primary aim is not to assess statistical significance, which would be unreliable in small sample size designs such as SCED, but instead to interpret the direction and magnitude of observed effects. We will use previously validated benchmarks to classify effect sizes as small (0.20‐0.59), moderate (0.60‐0.79), or large (≥0.80) [53]. Even small effect sizes will be considered potentially meaningful when supported by consistent patterns observed through visual inspection of the data (see Table 2).

**Table 2. T2:** Five visual analysis measures of comparison typically used for single-case experimental design evaluation.

Measure	Definition
Nonoverlap of all pairs (NAP)	Values from baseline and intervention time points are paired, and a percentage of pairs whose values do not overlap is calculated.
Extended celeration line (ECL)	An NAP that controls for positive trends in the preintervention phase by calculating the proportion of postintervention data points that are above the median trend line plotted from preintervention data.
Improvement rate difference	It is calculated as the difference in the rates of increase in outcome variable data between the preintervention and postintervention phases by dividing the number of “improved data points” by the total number of data points in that phase.
Tau-U	Tau-U adjusted pairs each preintervention and postintervention observation to make n pairs. The number of positive-change, negative-change, and tied pairs is calculated for each outcome variable
Percentage of nonoverlapping data, corrected (PNDC)	Particularly useful when anticipating an increase in the outcome variable postintervention, PNDC locates the highest data point in the preintervention phase and calculates the percentage of postintervention data points that exceed it. A data correction procedure is used to control for an upward preintervention trend.

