While evaluation of safety planning interventions is key to improving effectiveness and widespread implementation, RCTs in this space are exceedingly complex due to the important safety considerations and privacy concerns regarding women who are currently experiencing IPV [16-18]. Moreover, RCTs are expensive, complex studies that require large numbers of participants, and people experiencing IPV constitute a hard-to-reach population [19]. This places them out of reach for many community-based organizations that wish to evaluate innovative, survivor-centered programming but lack the scientific expertise and resources to conduct fully powered clinical trials. Moreover, many RCTs of safety planning interventions show null effects between intervention and control groups, which is hypothesized to be due (in part) to an intervention effect in the control group—that is, asking women in the control group about their IPV constitutes an intervention in and of itself, potentially blunting the true effect of the safety planning intervention [20,21].

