The baseline interview is designed to last approximately 15 to 20 minutes and will end with a reminder that the participant will complete some of these same measures every 3 to 4 days for the next 2 to 3 weeks until stability is reached. Participants will receive CAD $10 (US $7.15) as an online gift card or through electronic money transfer upon finishing each preintervention interview. Following the established safety protocols for working with those experiencing IPV described above, preintervention baseline assessments can occur via telephone, in person, or via an online survey, using the mode that seems the safest for the participant [46]. For telephone-based assessments, we will also ask the participant before beginning each session if she is in a private space. Whether collected remotely or in person, the SCED data will be recorded via Zoho Survey (Zoho Corporation) and saved directly to a secure Zoho server.

After each participant’s fifth baseline interview, the research team will assess the overall score for each outcome measure. If the participant achieves stability, measured using previously cited criteria wherein at least 85% of preintervention data fall within a 15% range of the median for at least 1 primary outcome measure (Patient Health Questionnaire-4 [PHQ-4], Measure of Victim Empowerment Related to Safety [MOVERS], and Decisional Conflict Scale), they will progress to the intervention interview [47,48]. If stability is not reached after 5 assessments, baseline measurements will continue for 2 more weeks (3 additional baseline measures with CAD $10 (US $7.15) compensation at each assessment) and reassessed. If, at this point, the participant’s outcome measures are deemed stable, they will proceed to the intervention interview. If not, they will still advance to the intervention visit, but their data will not be included in the effectiveness evaluation. Using the standard SCED protocol, these assessments will result in at least 5 but no more than 8 baseline measurements, ensuring that every participant receives the intervention as soon as possible [49].

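### Adjusted Tau-U does not correct for any baseline trend: with no app effect, a trend that simply continues is still graded moderate or small, depending on baseline length

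*Protocol article*

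**What the plan says.** The Data Analysis Plan introduces the metric with a general claim: "Tau-U allows for the estimation of intervention effects while accounting for trends that may be present during the baseline (preintervention) phase". For each woman and outcome it lists three quantities: Tau within the baseline, unadjusted Tau-U, and "adjusted Tau-U (A vs B), which corrects for any nonrandom trends in the baseline phase". No formula or denominator is given. Table 2 describes adjusted Tau-U through cross-phase pairs only and mentions no trend term.

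Values are graded small from 0.20, moderate from 0.60 and large from 0.80, with one set of cut-offs for every woman. Significance testing is set aside in favour of direction and magnitude, and "Even small effect sizes will be considered potentially meaningful when supported by consistent patterns observed through visual inspection of the data".

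On series length, Preintervention Assessments says "these assessments will result in at least 5 but no more than 8 baseline measurements", and Postintervention Interviews says "All participants will complete the same number of postintervention assessments (n=8) over the course of 4 weeks after their intervention interview". A woman moves to the intervention once "at least 85% of preintervention data fall within a 15% range of the median" on at least one listed outcome.

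**The concern.** Each woman is her own control, so the inference rests on separating an app effect from whatever was already happening during the baseline. The quoted clause tells the reader that the adjusted figure has done this.

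A baseline drift is plausible here. The Introduction argues, as a partial explanation of null randomised trials, that "asking women in the control group about their IPV constitutes an intervention in and of itself". In this study the same questions recur every 3 to 4 days before the app is seen. If part of a continuing drift stays in the adjusted figure, a reader who trusts the clause could credit the app with the effect of being asked. Because baseline length differs between women, the same drift could also receive different grades.

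**Working it through.** The article reports no Tau-U value, so there is no stated figure to reproduce. The check applies the definition to a case whose true effect is zero.

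**Inputs.** Baseline points nA = 5 to 8 (Preintervention Assessments; 5 or 8 as scheduled, and 6 or 7 if additional visits are missed). Postintervention points nB = 8 (Postintervention Interviews). Cut-offs 0.20, 0.60 and 0.80 (Data Analysis Plan). Assumption: the standard baseline-adjusted form, because the article names none.

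**Formulas.** S counts pairs that move towards benefit minus pairs that move away.
- Standard form: (S_AB − S_A) / (nA × nB)
- Alternative denominator: (S_AB − S_A) / (nA × nB + nA(nA − 1)/2)

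**Noise-free trend that continues, no app effect.** Every pair is ordered, so S_AB = nA × nB, S_A = nA(nA − 1)/2 and unadjusted Tau-U = 1.00 throughout. A full correction would give 0.

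| nA | S_AB | S_A | Standard form | Grade | Alternative denominator | Grade |
|---|---|---|---|---|---|---|
| 5 | 40 | 10 | 30/40 = 0.75 | moderate | 30/50 = 0.60 | moderate |
| 6 | 48 | 15 | 33/48 = 0.69 | moderate | 33/63 = 0.52 | small |
| 7 | 56 | 21 | 35/56 = 0.625 | moderate | 35/77 = 0.45 | small |
| 8 | 64 | 28 | 36/64 = 0.56 | small | 36/92 = 0.39 | small |

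A fuller form that adds the 28 ordered postintervention pairs gives (40 + 28 − 10)/78 = 0.74 at nA = 5 and (64 + 28 − 28)/120 = 0.53 at nA = 8. None of these forms gives 0. Tau on residuals from the Theil-Sen baseline line, projected over both phases, gives 0.00 at every nA.

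**Range.** With nA × nB as denominator the maximum is 1 + (nA − 1)/(2 × nB): 1 + 4/16 = 1.25 at nA = 5 and 1 + 7/16 = 1.44 at nA = 8. With the alternative denominator it is 1.

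**With noise** (simulation: unit-SD normal noise, linear drift over all visits, no effect, standard form, nA = 5). At an assumed drift of 0.2 SD per visit, mean unadjusted Tau is 0.61 and mean adjusted Tau-U 0.55 to 0.56, so the adjustment removes roughly a tenth. About half the series reach 0.60 (49% to 51% across runs). At 0.1 SD per visit 23% do; with no drift, 5%.

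**Stability rule.** Read as ±15% of the median, the baseline 57, 54, 50, 47, 43 passes: the median is 50 and the largest deviation 7/50 = 14%. Read as a band 15% wide (±7.5%), that series fails but 53, 52, 50, 49, 47 passes, with a largest deviation of 3/50 = 6%. Tau-U uses order only, so either monotone series can score 0.75 if it continues. Only one outcome has to be stable; the others may trend freely.

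**The case against.** Adjusted Tau-U is not the plan's only protection. Baseline Tau is reported beside it, fitted trend lines are drawn for both phases, and Table 2 lists an extended celeration line and a corrected nonoverlap percentage, each with some trend control. Study Limitations promises several estimators and assigns the corrected nonoverlap percentage to test bias. A reader might therefore infer too much in saying that reactivity will be reported as a moderate or large app effect. The documents do not support that: these displays can reveal a continuing trend. What they do not do is change the Tau-U grade, because no rule links them to it. Table 2 also frames both trend-controlled measures for an upward trend, whereas the study objectives expect decisional conflict and depressive symptoms to fall.

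Three further points stand.
- A reader might infer that a continuing trend is always graded moderate. It is not: at 8 baselines the noise-free grade is small in every form tried.
- A reader might infer that the index exceeds 1. That belongs to the nA × nB denominator, which the article does not state and a fuller plan might settle.
- The drift size is an assumption. The Introduction says that asking can act as an intervention; it does not say that change is linear or persists undiminished through follow-up.

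The study is also described as preliminary and not expected to generalise. That limits the consequence but does not make the clause true.

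**Conclusion.** The clause is wrong as written. Under every Tau-U form tried, a baseline trend is only partly reduced. The standard form leaves 0.75 to 0.56 where the true effect is zero, and the alternative denominator leaves 0.60 to 0.39. Since the plan allows small grades to count as meaningful, the result at 8 baselines is not harmless either. The same null trend also receives different grades by baseline length under one set of cut-offs.

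The noise-free figures follow from the definition and the planned visit numbers alone. The figure of about half rests on the standard form, 5 baselines and an assumed drift of 0.2 SD per visit. The conclusion concerns the clause and the grade attached to the adjusted figure. It does not show that the study's overall reading must be mistaken.

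**What to change.** - Delete the claim that adjusted Tau-U corrects for any baseline trend. Name the variant and denominator, and state that it only partly reduces such a trend and is not graded as a trend-free effect.
- Report unadjusted Tau beside a trend-projecting measure: Tau on residuals from the Theil-Sen baseline line, or the planned celeration line applied in the direction of benefit. The celeration line yields a proportion, so the Tau cut-offs do not carry over and its threshold must be set in advance.
- Where baseline Tau runs towards benefit, attribute a grade to the app only if both measures reach it. Otherwise report *not separable from baseline trend*.
- Do not grade baseline-corrected Tau alone: with no trend and no effect it reaches 0.60 in 32% of series at 5 baselines. Do not rely on agreement in direction alone: at 0.2 SD drift both measures favour benefit in 49% of null series.

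The cost is one paragraph, a few lines of code and no new data. Results says that four participants are already analysed, so they need re-running and the change should be recorded as made after that analysis.

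The limit must be stated too. Baseline-corrected Tau has a null SD of about 0.73 with 5 baselines and 0.60 with 8. Requiring both measures at 0.60 or more still leaves about 24% false moderate-or-higher grades (5 baselines, 0.2 SD drift), against about half for adjusted Tau-U. Fewer effects will be called.
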